# Development and Economic Evaluation of a Patient-Centered Care Model for Children With Duchenne Muscular Dystrophy: Protocol for a Quasi-Experimental Study

**DOI:** 10.2196/42491

**Published:** 2023-04-28

**Keywords:** Duchenne muscular dystrophy, patient-centered care, disabilities, quality of life, caregivers, cost of illness, effective, treatment, policy, caregiver, pediatrics, intervention, psychological, disability

## Abstract

**Background:**

Duchenne muscular dystrophy (DMD) is a rare progressive muscular disease that primarily affects boys. A lack of comprehensive care for patients living with DMD is directly associated with a compromised quality of life (QoL) for those affected and their caregivers. This disease also has a huge economic impact on families as its treatment requires substantial direct, indirect, and informal care costs.

**Objective:**

This study presents a protocol developed to evaluate the feasibility and efficacy of a patient-centered care (PCC) model for children with DMD. The care model was designed with the aim to empower families, improve QoL, and reduce economic burden on their families.

**Methods:**

This study is planned as a quasi-experimental study that will enroll 70 consecutive families with boys (aged 5-15 years) with DMD visiting a tertiary care center. The study is being conducted in 2 phases (preintervention and postintervention phases, referred to as phase 1 and phase 2, respectively). During phase 1, the patients received routine care. The study is now in phase 2, with the intervention currently being administered. The intervention is based on the PCC model individualized by the intervention team. The model has a comprehensive DMD telecare component that includes teleconsultation as one of its key components to reduce in-person physician visits at the health facility. Teleconsultation is especially beneficial for late-ambulatory and nonambulatory patients. Data on economic burden are being collected for out-of-pocket expenses for both phases during in-person visits via telephone or messaging apps on a monthly basis. QoL data for patients and their primary caregivers are being collected at 3 time points (ie, time of enrollment, end of phase 1, and end of phase 2). Outcome measures are being assessed as changes in economic burden on families and changes in QoL scores.

**Results:**

Participant recruitment began in July 2021. The study is ongoing and expected to be completed by March 2023. The findings based on baseline data are expected to be submitted for publication in 2023.

**Conclusions:**

This paper outlines a research proposal developed to study the impact of a PCC model for patients with DMD in low- and middle-income countries (LMICs). This study is expected to provide evidence of whether a multicomponent, patient-centric intervention could reduce economic burdens on families and improve their QoL. The results of this study could guide policy makers and health professionals in India and other LMICs to facilitate a comprehensive care program for patients living with DMD. The economic impact of a rare disease is an important consideration to formulate or evaluate any health policy or intervention related to new treatments and financial support schemes.

**Trial Registration:**

Clinical Trials Registry India (ICMR-NIMS) CTRI/2021/06/034274; https://www.ctri.nic.in/Clinicaltrials/pmaindet2.php?trialid=56650

**International Registered Report Identifier (IRRID):**

PRR1-10.2196/42491

## Introduction

### Background

Duchenne muscular dystrophy (DMD) is an X-linked recessive disease with an incidence of 1 in 3500 to 6000 live male births [1]. It progresses from an ambulatory to a nonambulatory stage, with the child usually becoming wheelchair-bound between 11 and 13 years and death occurring in the late teens or early twenties [2-4]. Even with this short span of life, children with DMD face many challenges, as their progression through various transitional phases impacts not only them but also their families and society at large [5].

The progressive and irreversible damage to the muscles results in weakness, loss of ambulation, breathing issues, and cardiomyopathy. Currently, there is no definitive treatment to halt the disease’s progression. Disease management mostly revolves around symptom management and involves a multidisciplinary approach to address various systemic complications [6].

### Course of Disease

Boys with DMD usually remain asymptomatic up to 2 years of age and get diagnosed between 4 to 6 years of age. Most of the boys with DMD are limited to assisted ambulation with the help of long leg braces by the age of 10 years. Age of loss of ambulation globally is between 13 and 14 years, whereas in resource-limited settings, it is between 9 and 11 years [4]. There is no study on the prevalence or incidence of DMD in India. However, a study from southern India [7] on 275 genetically confirmed patients with DMD was conducted to study the natural course of motor milestones. Authors reported the mean age of onset of symptoms was 3.7 years, and the mean age at presentation was 8.1 years. During the follow-up period of 15 years, 155 out of 275 (56.4%) children had either become wheelchair-bound or bed-bound or died. The affected children were wheelchairs bound by a mean age of 10.4 years and bed-bound by 11.8 years. Seven boys (2.6%) died during the follow-up period at a mean age of 15.2 years.

DMD requires a multidisciplinary team approach for holistic management. This includes diagnostic services, physical therapy, orthotics, respiratory therapy, corrective orthopedic surgery, ventilation, feeding support, and speech therapy. Muscle degeneration can be slowed down with the use of corticosteroids, while antibiotics may be needed for respiratory infections [8-11]. Occupational therapy, assistive devices, and a wheelchair are also beneficial to the children. Some patients may need a pacemaker for cardiac abnormalities and assisted ventilation for respiratory muscle weakness. Patients diagnosed with DMD should expect to make a successful transition to adulthood, which includes education, health care, and social support to transition smoothly from adolescence to adulthood [12,13]. 

The DMD Care Considerations Working Group identified eleven components of care: (1) diagnosis, (2) neuromuscular management, (3) rehabilitation management, (4) gastrointestinal and nutritional management, (5) respiratory management, (6) cardiac management, (7) orthopedic and surgical management, (8) psychosocial management, (9) primary care and emergency management, (10) endocrine management (including growth, puberty, adrenal insufficiency, and bone health), and (11) transitions of care across the life span. The mainstay of management is still limited to physiotherapy and glucocorticoids therapy, which help in delaying loss of ambulation, an important milestone of the disease [6,14]. Treatment modalities also have changed, especially with the advent of exon-skipping therapy and gene editing tools. However, these new modalities of treatment have not made a significant clinical impact yet [15].

### Empowering Patients and Caregivers

Globally, we are witnessing a new paradigm shift to resolve problems from a mechanistic or Newtonian worldview to a holistic view. This approach involves human values, creativity, and evolution, and it has affected the approach toward understanding human health. Nevertheless, the reductionistic approach dominates the imagination of the scientific fraternity [16]. The biomedical or reductionistic approach sees patients as an isolated problem, whereas we need to understand that a holistic approach (ie, social, economic, sanitary, environmental, and political commitment) is needed to manage a disease.

An inclusive paradigm has two major components: (1) self-empowerment of the patient and (2) holism. Empowering patients involves developing skills, control over resources, ensuring autonomy in decision-making, and taking ownership of their health [17,18].

Empowering patients through an effective health care delivery model has the potential to improve the cost-effectiveness of care, especially for people affected by long-term conditions [19]. Patient-centered care (PCC) increases adherence to disease management, reduces loss to follow-up in the health care system, and, in turn, reduces morbidity and improves quality of life (QoL) for patients [17].

### QoL of Children Living With DMD

With the advancement in medical management, patients with DMD are reported to live longer up to the third decade of life. These require more years to live with functional disability and more years of caregiving. Past studies have reported variable QoL among patients with DMD, with some studies showing poor QoL and others showing no difference between healthy children and those with DMD. Being able to participate in various activities of daily living, like personal care, mobility, social relationships, education, recreation and leisure, spirituality, and community life, are outcomes of health. Physical disability substantially decreases participation and consequently impairs QoL [18]. Studies have reported that only physical participation levels were much lower in patients with DMD, and other participation levels were almost the same.

Bendixen et al [20] compared participation in life activities and perceived QoL between younger and adolescent boys with DMD and age-matched controls. No differences in perceived QoL were observed between the participants with DMD and the healthy controls, but the older adolescent participants with DMD had significantly lower QoL subscales of physical, social, and total composite scores. de Moura and colleagues [21] studied the relationship between physical dependence and QoL of patients with DMD and the QoL and burden of caregivers. Lower QoL was observed in caregivers with increased age and the burden of caregiving. In a review, Landfeldt et al found [22] the informal care of patients with DMD was associated with a substantial burden, and they recommended further research to better understand the relationship between clinical implications and progression of disease and caregiver burden. A cross-sectional study by Jackson et al [23] examined mothers’ demographic characteristics and their sons’ QoL-related factors to identify which ones contribute to poorer health-related QoL and greater emotional distress. Mothers’ perception of their sons’ health-related QoL is a significant predictor of their own health-related QoL and emotional distress. In turn, mothers’ physical and emotional health influences their social activities. Social activities are important to manage stress among caregiving parents. QoL is a measure used to obtain additional information on the effectiveness of clinical measures, the quality of services they need for health care, the effectiveness of the interventions, and cost-utility analyses. Change in QoL reflects how much a patient is satisfied with his or her treatment or the system of health care delivery [20,24,25].

### Economic Burden of Disease

Previous studies have revealed that DMD also has a substantial economic burden on families. Studies have shown that this burden increases markedly with disease progression; however, no such study has been conducted in the Southeast Asian region [22,26].

Health care delivery systems frequently use patient engagement to reduce expenditure and improve health outcomes. When analyzing the health care delivery system in the state of Minnesota, Hibbard et al [27] concluded that patients who were less actively engaged in their treatment had 8 times higher health care costs in the first year, and this was significantly different from patients who were actively engaged in their treatment. Another review by Hibbard and Green [28] on patient engagement concluded that various tailor-made interventions to increase patient involvement in their disease significantly improved health outcomes. Nevertheless, very few studies comment on costs related to disease. Proper allocation of resources is most important for any institution to have sustainable development, and this applies to the health care system as well. Cost-of-illness studies can provide important information to policy makers at both the micro (eg, cost-effectiveness of new interventions) and macro level (eg, fund allocation for further research and prioritization of disease for preventive interventions) [13,29-31].

The Indian Ministry of Health and Family Welfare has begun to address this issue related to rare diseases, as reflected in its 2017 National Health Policy. The Indian government approved the separate National Rare Disease Policy in 2021. This policy recommends a focusing on indigenous research and local production of medicines, searching for low-cost treatments for rare diseases, and screening and early detection. Financial support is sought to be given to the rare diseases classified as Group 1 in the policy under the umbrella of Rashtriya Arogya Nidhi or Pradhan Mantri Jan Arogya Yojana. However, DMD is classified under Group 3, described as “diseases for which definitive treatment is available but challenges are to make optimal patient selection for benefit, very high cost and lifelong therapy” [32]. The policy identified 8 tertiary care centers as Centers of Excellence for managing rare diseases. The hospital-based National Registry of Rare Diseases was created in these centers to ascertain the exact burden of rare diseases.

Accordingly, this study aims to estimate the economic burden incurred by the families of children with DMD seeking care at a government hospital. Next, we aim to develop a PCC model (intervention) to build the capacity of affected families to cope with DMD, thus reducing the financial burden on families. Finally, we aim to compare the impact of intervention with routine care on QoL (caregiver and patient) and economic burden after 6 months of intervention.

## Methods

### Study Design

This is a longitudinal quasi-experimental study that will be conducted in 2 phases. It is important to note that within the scope of this study, it is difficult to achieve a controlled experimental design. There is no randomization, and the same group of subjects are to be compared before and after the intervention. The experimental condition may be systematically different across the time frame. Considering this limitation, we chose a quasi-experimental design for this study. [33]

Phase 1 of the study is observational, and no intervention is administered. Participants (previously diagnosed and under follow-up as well as new patients) were recruited prospectively from pediatric neurology clinic, department of Pediatrics, Advanced Pediatrics Center, Post Graduate Institute of Medical Education & Research (PGIMER), Chandigarh, India. Detailed information about the study was provided to the children and their caregivers. After providing consent to participate in the study, the primary caregivers were interviewed for demographic information, clinical information, and information related to their economic status and financial burden of disease caused by DMD. The QoL of patients and caregivers was assessed with the EuroQoL 5-Dimension 5-Level (EQ-5D-5L) scale and the World Health Organization Quality-of-Life Scale (WHOQOL-BREF), respectively. After recruitment into the study, the patients were followed up for 6 months. Routine treatment as per institutional norms was given during this period. The primary caregiver was contacted via telephone monthly for data collection on economic burden. After the 6 months, the participants entered into the next phase (ie, phase 2).

Parallelly, during phase 1, the PCC intervention model was developed. The rationale behind developing the care model was to provide basic information about DMD and treatment options to the patients and their parents or caregivers so that they could participate effectively in the process of obtaining comprehensive care in a resource-limited setting. The intervention includes information about the disease, an instructional booklet, and a workbook to encourage compliance. This study also includes a teleconsultation with pediatric neurologist and the rehabilitation team. The sessions are designed to facilitate caregivers in decision-making through active participation in every stage of the disease. This set of interventions are collectively referred to as the Comprehensive DMD-Telecare Model.

Phase 2 is the interventional phase of the study, which commences once the patient has completed phase 1 (ie, the first 6 months of the study). During phase 2, patients and their parents or caregivers are given a set of interventions developed during phase 1. The patients are followed up prospectively for the subsequent 6 months (Figure 1), and data on economic burden are recorded telephonically on monthly basis. Children are visiting the health facility just twice during the follow-up period (ie, at the beginning and at the end of phase 2). This reduced the number of in-person visits the patients had to make to the health facility.

**Figure 1 figure1:**
[figure not shown]
Overview of study design. DMD: Duchenne muscular dystrophy; OPD: Outpatient Department; PCC: patient-centered care; QoL: quality of life.

### Ethics Approval

Approval for this study was granted from the ethics committees of PGIMER (IEC-01/2021-1884) and Lovey Professional University (LPU/IEC/2021/01/24). The patients and their caregivers were informed about the study and provided consent before recruitment. Information collected from the patients and their caregivers will be anonymized. The study protocol was registered with the Clinical Trials Registry India (CTRI/2021/06/034274).

### Setting and Sample Size Considerations

Patients were recruited prospectively in a consecutive manner from the Pediatric Neurology Clinic of the Advanced Pediatric Center at PGIMER in Chandigarh, India. This institute caters to approximately 7 north Indian states, namely, Punjab, Haryana, Himachal Pradesh, Jammu and Kashmir, Uttarakhand, Bihar, the northwestern part of Uttar Pradesh, and the Union Territory of Chandigarh.

The sample size estimation for the primary outcome was in accordance to changes in patients’ health-related QoL (HRQOL) questionnaire scores. The QoL scores were assessed in the observational phase (0-6 months) and compared with the QoL scores in the intervention phase (7-12 months). A clinical meaningful difference based on the minimum important difference from HRQOL was 0.1 [34], along with an SD of 0.2 [35] and an allocation ratio of 1:1. The estimated sample for the study was 126 (63 patient in each phase) to achieve a level of significance of 95% CI at a power of 80%, accounting for a 10% dropout rate. The total sample size was 140, with 70 patients in each phase.

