## Results

Study enrollment was completed in March 2022 with a total of 100 children with DMD and their caregivers (125% of the target). All 100 patients and their caregivers were followed up for 6 months in phase 1 of the study, which was completed in July 2022. The intervention was administered to 66 patients and their caregivers (94.3% of the target population) in phase 2. The participants were further followed for the subsequent 6 months, and phase 2 ended in December 2022. We are in the process of data entry and data cleaning. Initial data show that the children range in age between 5 and 15 years at enrollment, with a mean age of 8.3 (SD 1.9) years. Most of the children (56/100, 56%) enrolled in this study are in the late ambulatory disease (stage 3), and only 1 (1%) child was in a late nonambulatory stage at the time of enrollment. However, these dynamics changed swiftly with the progression of the disease.

Primary caregivers enrolled (n=100) at the baseline in the study were mostly mothers (58/100, 58%), with fathers comprising 38% (38/100) of the caregivers. Only 57% (57/100) of caregivers had some knowledge about DMD before enrollment. About 75% of the caregivers were educated more than high school, and 8.2% of them did not receive any formal education. More than half (51/100, 51%) the patients were had upper-middle SES, and (3/100, 3%) had lower SES. Because this study is only in the data entry and data cleaning phase, no impact data are available to report on the study objectives, aims, and hypotheses. The findings are expected to be published in 2024.

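### The sample size is worked out for two independent groups, but one group of children is compared with itself, so the totals of 126 and 140 and the 80% power do not describe this design

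*Protocol article*

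**What the plan says.** Setting and Sample Size Considerations takes a minimum important difference of 0.1 in the quality-of-life score, "along with an SD of 0.2 [35] and an allocation ratio of 1:1". The significance level is expressed through a 95% confidence interval, the power is 80%, and dropout is put at 10%. The result is stated as follows: "The estimated sample for the study was 126 (63 patient in each phase"). The 10% dropout is mentioned in that same sentence. The paragraph then closes with a larger figure: "The total sample size was 140, with 70 patients in each phase".

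Study Design describes something else: "There is no randomization, and the same group of subjects are to be compared before and after the intervention". The same section has each patient enter phase 2 after completing six months of phase 1, and the Discussion repeats that a single group is compared. Data Management and Analysis lists a paired t test. The Abstract says that the study "will enroll 70 consecutive families with boys".

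Results reports enrolment "with a total of 100 children with DMD and their caregivers (125% of the target") and, in the same paragraph, 66 children given the intervention, described as 94.3% of the target population.

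**The concern.** An allocation ratio and a total of two equal parts belong to a trial in which different patients supply the two means. Here the same children supply both. The precision of a before-after comparison depends on the SD of the within-child change, or equivalently on the cross-sectional SD and the correlation between a child's two scores. The document gives an SD of 0.2 without saying that it is an SD of change, and gives no correlation.

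This is the only sample-size justification, and it is for the primary quality-of-life outcome. As printed, a reader cannot tell what power the study has for its own comparison. That will matter most if the result is null. The total of 140 also does not match the number of families to be enrolled, and Results uses two different targets in one paragraph.

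**Working it through.** **Inputs.** From Setting and Sample Size Considerations: difference 0.1, SD 0.2, ratio 1:1, 95% confidence level (taken as two-sided 5%; the sides are not stated), power 80%, dropout 10%. From Results: 100 enrolled, 66 given the intervention. Not in the document: the within-child correlation ρ, which is shown below as an assumed range.

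**Step 1: reproduce the plan's figures.** Two independent means, normal approximation:

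n per group = 2(1.960 + 0.842)² × (0.2/0.1)² = 62.8, rounded up to 63; total 126.

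With 10% dropout: 63/0.9 = 70 and 126/0.9 = 140. Power with 63 per group is 80.1%. All four stated counts reproduce. The sentence that gives 126 also says it accounts for dropout, but 126 is the figure before dropout and 140 the figure after.

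**Step 2: paired comparison of scores at the end of phase 1 and the end of phase 2.** SD of change = 0.2 × √(2(1 − ρ)). Power is from the noncentral t distribution for a paired t test.

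| Assumed ρ | SD of change | Completers for 80% | Power, 63 children | Power, 66 children |
|---|---|---|---|---|
| 0 | 0.283 | 65 | 79% | 81% |
| 0.3 | 0.237 | 46 | 91% | 92% |
| 0.5 | 0.200 | 34 | 97% | 98% |
| 0.7 | 0.155 | 21 | >99% | >99% |

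If 0.2 was meant as the SD of change, the ρ = 0.5 row applies: 34 completers (32 by the normal approximation), not 63.

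**Step 3: difference between the two six-month changes.** The primary outcome measure in the study outcomes textbox can also be read as the change over months 0-6 against the change over months 7-12. The contrast is then Y₁₂ − 2Y₆ + Y₀. If all three pairs of visits have the same correlation (compound symmetry), its SD is 0.2 × √(6(1 − ρ)), which is three times the variance in Step 2.

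| Assumed ρ | SD of contrast | Completers for 80% | Power, 66 children |
|---|---|---|---|
| 0 | 0.490 | 191 | 37% |
| 0.3 | 0.410 | 134 | 50% |
| 0.5 | 0.346 | 97 | 64% |
| 0.7 | 0.268 | 59 | 85% |

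Power with 66 reaches 80% at ρ of about 0.66. Under a first-order autoregressive structure the variance is 0.2² × 2(1 − ρ)(3 − ρ), so the ratio to Step 2 is 3 − ρ. At adjacent-visit ρ = 0.5 the ratio is 2.5 and power with 66 is 72%; 80% is reached at about 0.58.

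**Step 4: the targets.** 66/70 = 94.3%, so that percentage uses 70. 100/1.25 = 80, so the other implies 80. Against 70, 100 would be 143%.

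**The case against.** The strongest defence is that the error does no harm. The sample-size paragraph compares scores in one phase with scores in the other, and 0.1 is an important difference in a score. On that reading the independent-groups figure is a safe one for a paired design, since any positive correlation pushes power above the stated value. This stands.

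A reader might infer from Step 3 that the study is underpowered. The document does not support that. Low power requires the change-against-change reading of an ambiguous outcome measure, together with a moderate or low correlation, and the figures also depend on the correlation structure.

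Two other inferences go too far. One is that 63 can come only from the two-group formula. The paired normal formula with ρ = 0 also gives 63, although the 1:1 ratio and the doubled total make the two-group formula the likely source. The other is that 140 children were planned. The document never says so; read with Study Design and the Abstract, 140 is 70 children counted once per phase, and the intended target can be recovered as 70.

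It is also fair to say that the basis of the 125% is not given, so it cannot simply be replaced by 143%.

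None of this makes the printed calculation fit the design. The allocation ratio has no meaning here, the totals are not numbers of patients, and the SD that a paired test needs is missing.

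**Conclusion.** The point holds as an error in the stated calculation, not as a demonstrated shortage of patients. The counts 63/126 and 70/140 are arithmetically right for two independent groups, which this study does not have. The totals are twice the number of children, and 80% is the power of the planned comparison only if a child's two scores are nearly uncorrelated.

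For end-of-phase scores, power with 66 children runs from about 81% to over 99% for assumed correlations of 0 to 0.7, so the stated figure is too low for any appreciable positive correlation. For a difference of six-month changes it would be about 37% to 85% over the same range under compound symmetry, and somewhat higher under an autoregressive structure at positive correlations. All of these take 0.2 as the cross-sectional SD at every visit and a two-sided 5% test. The correlations are assumptions, because the document supplies none.

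The 125% and 94.3% in Results imply targets of 80 and 70 and cannot both refer to the same one.

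**What to change.** In Setting and Sample Size Considerations:

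- Restate the calculation for one group with paired measurements and name the contrast: end-of-phase scores or the difference between six-month changes.
- Give the SD of within-child change for that contrast, or the SD of 0.2 with an assumed range of correlations, and the resulting power for 63 completers out of 70 enrolled.
- Delete the 1:1 allocation ratio and the totals of 126 and 140.
- Attach the 10% dropout allowance to 70, not to 63.
- State one target of 70 families, as in the Abstract.

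In Results, reconcile the 125% with the 94.3% by saying which target each uses.

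The cost is rewording one paragraph and checking one percentage. No more patients are needed. Results says that no impact data are available yet, so the contrast can still be named before the outcome is reported.
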